### Electromyography signal processing

The root mean square (RMS), median frequency, asymmetry index and co-contraction index will be used as the parameters for the interpretation of the signal processing. The signals will be processed using specific routines developed with the aid of the Matlab program, version 7.1 (The MathWorks Inc., Massachusetts, USA). The RMS of the signal (expressed in μV) obtained at rest and during MHC will be normalized by the largest RMS obtained during three readings of MVC (μmV/μV × 100: %MVC). With the mandible at rest, the RMS will be calculated for the entire 15 s of the signal collected. Data on MHC will be analyzed based on Ferrario *et al*. [18], with the first and last second of the raw EMG signal being discarded and the RMS being calculated using a 25-ms moving window without overlap for the 3 s of signal selected.

The overlap percentage coefficient (OPC, unit: %) described by Ferrario *et al*. [18] will be used to evaluate the distribution of muscle activity in time and the amplitude determined by the occlusion. Symmetric distribution of muscle activity determined by the OPC will be analyzed considering variability between 0% (absence of symmetry) and 100% (perfect symmetry). Lateral excursion (potential given by imbalanced contractile activities of the contralateral masseter and temporal muscles) will be evaluated using the torque coefficient (TC, unit: %) considering variability between 0% (absence of lateral excursion force) and 100% (maximum lateral excursion force).

The EMG signal of the paired muscles under each situation recorded during MHC will be compared by calculating a percentage of OPC and TC. Mean normalized EMG activity (%MVC) of the right and left masseter and temporal muscles will be calculated and used for comparisons among evaluation times (pre-treatment, immediate post-treatment and late post-treatment).

### Visual analog scale

A visual analog scale (VAS) allows the quantification of pain intensity. This scale consists of a straight line measuring 10 cm in length, with ‘absence of pain’ written at one end and ‘worst pain ever felt’ written at the other end. The volunteer will be instructed to make a perpendicular line between the two extremes that represents the pain level he/she is feeling at the time [19].

### Algometry

A digital algometer (DD-200, Instrutherm™) will be used to evaluate pain through the application of pressure. For such, the volunteer will be seated in a chair, trunk erect, back completely supported, feet on floor and hand on thighs, respecting the Frankfurt plane. The researcher will position the algometer and apply gradual pressure at three points over the masseter muscle (upper, middle and lower), three points over the temporal muscle (posterior, middle and anterior) and over the lateral pole (bilaterally) based on the findings of the clinical exam (palpation) of the RDC/TMD. Pressure will be applied to all points until the volunteer reports feeling pain. The value registered on the display of the algometer will then be recorded. If the volunteer does not feel pain, maximum pressure will not exceed 4 Kgf [20]. Pressure will be applied using the rubber tip measuring 1 cm^2^ in direct contact with the skin at the ‘fast’ velocity of the ‘peak hold’ function (specification of the DD-200 digital algometer, Instrutherm™). Prior to the readings, the algometer will be applied to the volunteer’s arm to familiarize him/her with the procedure. The volunteer will be instructed to raise his/her hand to indicate the exact instant of pain, at which point the researcher will cease to apply the pressure. The algometer will be applied only once to each of the aforementioned points and a 30-s rest interval will be given between readings.

### Phototherapy

The portable PainAway™ nine-diode cluster (Multi Radiance Medical®, Solon, OH, USA) will be employed. This system has one 905 nm laser diode, four 875 nm LED diodes and four 670 nm LED diodes. The aperture size of device is 4 cm^2^ (Table 2).

**Table 2 Tab2:** **Phototherapy parameters**

Number of super-pulsed lasers	1 Super-pulsed laser
Wavelength (nm)	905
Frequency (Hz)	1000
Average optical output (mW)	0.9
Peak power (W)	8.5
Dose (J) total per group (20s, 40s, 60s)	0.018; 0.036; 0.054
Spot size (cm2)	0.4
Number of red LEDs	4 Red
Wavelength (nm)	640(±10 nm)
Frequency (Hz)	2
Average optical output (mW)-each	15
Dose (J) each emitter per group (20s, 40s, 60s)	0.3; 0.6; 0.9
Dose (J) total per group (20s, 40s, 60s)	1.2; 2.4; 3.6
Spot size (cm2)-each	0.9
Number of infrared LEDs	4 infrared
Wavelength (nm)	875(±10 nm)
Frequency (Hz)	16
Average optical output (mW)-each	17.5
Dose (J) each emitter per group (20s, 40s, 60s)	0.35; 0.70; 1.05
Dose (J) total per group (20s, 40s, 60s)	1.4; 2.8; 4.2
Spot size (cm2)-each	
Magnetic field (mT)	35
Treatment time (s)	20; 40 or 60
Aperture of device (cm^2^)	4
Total delivered energy (J) per point	2.62; 5.24 or 7.86
Total delivered energy (J) per individual	26.20; 52.40 or 78.60

For the blinding of the participants, the phototherapy equipment with the different light sources has two identical application hand pieces provided by the manufacturer - one with an active tip and the other for placebo applications (does not emit energy), but both with the same sound device. The tips will be denominated X and Y by a researcher who will not participate in the application or evaluations. The researchers who will administer the phototherapy procedures and those in charge of the evaluations will be blinded to which hand piece has the active effect and which is for the placebo application. The hand pieces will only be identified at the end of the data collection process. Table 2 displays the doses and application times for each group.

Phototherapy with the different light sources will be applied to two points of the masseter muscle bilaterally and three points on the temporal muscle bilaterally (totaling 10 application points), based on the results of the clinical exam performed using the RDC/TMD. The same points will be evaluated using an algometer.

Phototherapy will be applied by one of the researchers in an isolated room with only the researcher and the volunteer present. The researcher will receive the pre-programmed hand piece. Both the researcher and volunteer will be wearing eye protection equipment. The volunteer will be in the supine position on a cot with lower limbs supported on a roll of foam rubber measuring 20 cm in diameter and head supported on a pillow to provide a comfortable resting posture. Phototherapy will be applied using the point technique in contact with the skin with a beam area of 4 cm^2^ (device aperture). The placebo group will be submitted to the same procedures as the groups submitted to phototherapy. Only the coordinator will have knowledge regarding the different phototherapy and placebo applications. At the end of the study, the individuals in the placebo group will be submitted to treatment with active phototherapy.

### Sample size

The sample size was calculated considering α = 0.05 (5% chance of a type I error), 1-β = 0.95 (% of sample power) and data from a visual analog scale (VAS) reported in the study by Pereira *et al*. [21]. The minimum number for each group was determined to be 15 individuals, to which 20% was added to compensate for possible dropouts during the study (total: 18 individuals per group). This calculation was performed using the G*Power software program [22]. Seventy-two individuals will be allocated to different groups (18 individuals per group) through a randomization process involving opaque envelopes containing cards stipulating one of the three following groups: A (2.62 Joules), B (5.24 Joules), C (7.86 Joules) and D (0 Joules).

### Data analysis

Pain will be the primary outcome and will be determined using a VAS and algometer. EMG will be the secondary outcome. The independent variables will be the different light sources used for phototherapy. The dependent variables will be derived from the pre-treatment and post-treatment evaluations. Intra-group comparisons will be performed using repeated-measures analysis of variance (ANOVA or Friedman’s test), followed by either the Student’s t-test or Wilcoxon’s test. Inter-group comparisons will be performed using either one-way ANOVA or the Kruskal-Wallis test. The choice of tests will be determined by the distribution (normal or non-normal) of the data. The level of significance will be set to 5% (*P* <0.05). All comparisons and statistical analyses will be performed using the SPSS program, version 13.0 (Chicago, IL, USA). Cohen’s d will be employed to determine the clinical effect size of the proposed therapies, with the interpretation of the coefficients based on the classification established by Cohen [23]: 0.2 = small effect; ≥0.5 = moderate effect; ≥0.8 = large effect.

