**Methods/Design:**

A placebo-controlled, double-blind, randomized, clinical trial will be carried out involving 72 women between 18 and 40 years of age with a diagnosis of myogenous TMD. The participants will then be randomly allocated to four groups totaling 18 individuals per group. Three groups will be submitted to a single session of phototherapy with different light sources, and one group will receive placebo therapy: Group A (2.62 Joules); Group B (5.24 Joules); Group C (7.86 Joules); and Group D (0 Joules). The following assessment tools will be administered on four separate occasions (baseline and immediately after, 24 h after and 48 h after phototherapy). Pain intensity will be assessed using the visual analog scale for pain, while pain thresholds will be determined using algometer, and electromyographic (EMG) analysis on the masseter and anterior temporal muscles.

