## Background

According to the International Association for the Study of Pain (IASP) [1], the term temporomandibular disorder (TMD) regards a subgroup of orofacial pain, the symptoms of which include pain or discomfort in the temporomandibular joint, ears, masticatory muscles and neck on one or both sides, as well as joint sounds, limited mandibular movements or mandibular deviation and difficulties chewing. Muscle pain is one of the most common and limiting clinical manifestations of this condition [2–5]. The main causes of TMD are trauma involving local tissues, chronic repetitive microtrauma, non-habitual use of the mandible and an increase in emotional stress [6]. With regard to prevalence, it is estimated that 20% of the population worldwide have TMD, but only 10 to 20% of affected individuals seek some form of treatment [7, 8]. Phototherapy, such as low-level laser therapy (LLLT) and light-emitting diode (LED) therapy, is one of the resources used by dentists and physiotherapists to treat TMD. Due to the low energy intensity and wavelengths capable of penetrating biological tissues, LLLT is believed to influence the synthesis, release and metabolism of numerous signaling substances involved in analgesia [9, 10]. This resource is reported to lead to an increase in the level of beta-endorphins, a reduction in bradykinin, a reduction in the release of histamine, an increase in lymphatic flow, reductions in swelling and pain-related substances, an increase in blood supply, a reduction in the duration of inflammation and the induction of muscle relaxation [11, 12]. LED therapy has been used for the same purposes and has demonstrated similar results, while offering the advantages of a lower cost and greater equipment durability [13, 14]. However, an exhaustive review of the literature has revealed no studies involving the use of phototherapy with different light sources (LLLT and LED) on the same device for application to the masseter and temporal muscles in individuals with myogenous TMD. Knowledge regarding the clinical effects of these forms of phototherapy can contribute to the indication of the best therapeutic resource for such patients. the use of therapeutic appliances that combine different sources of light may be advantageous, especially as devices with this feature began to be available in recent years commercially, making it necessary to research primarily on effects and the choice of best parameters, primarily analyzing immediate effect to later assess cumulative dose effects on the masticatory muscles in patients with TMD.

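### Pain is primary on two instruments at three post-treatment times with no deciding instrument or time, so the stated 5% does not protect the main conclusion

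*Protocol article*

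**What the plan says.** The Data analysis section defines the primary outcome as follows: "Pain will be the primary outcome and will be determined using a VAS and algometer". EMG is secondary. For the comparison of groups it says: "Inter-group comparisons will be performed using either one-way ANOVA or the Kruskal-Wallis test". The error level is given once: "The level of significance will be set to 5% (*P* <0.05".

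The Abstract has the assessments made "on four separate occasions (baseline and immediately after, 24 h after and 48 h after phototherapy", and the Final evaluations section confirms the three post-treatment times. None of the three is called primary.

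The Algometry section lists "three points over the masseter muscle (upper, middle and lower), three points over the temporal muscle (posterior, middle and anterior", plus the lateral pole. It defines no summary over these sites. The Phototherapy section gives a different set, ten application points with two rather than three per masseter, and says that the algometer is used on those same points.

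The Sample size section uses alpha 0.05, power 0.95 and VAS data from a cited study. It does not mention algometry.

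**The concern.** A one-way ANOVA or Kruskal-Wallis test handles one variable at one time. With two primary instruments and three post-treatment times, the plan therefore yields at least six between-group tests of the primary outcome, and nothing says which one answers the trial's question. The protocol also does not say whether one significant instrument is enough or both are needed.

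As written, the trial could be called positive on whichever instrument and time falls below 0.05. The design was sized for one test of VAS at 5%, so the error rate that the sample size assumes is not the one that the main conclusion would have.

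**Working it through.** **Inputs from the protocol.** Four groups; 15 per group before the dropout allowance and 18 after it; alpha 0.05; power 0.95 (Sample size). Two instruments and a one-way test at 5% (Data analysis). Three post-treatment times (Abstract; Final evaluations). Algometer sites: (3 + 3 + 1) × 2 = 14 if the word for both sides covers all sites, 3 + 3 + 2 = 8 if it covers the lateral pole only (Algometry), or (2 + 3) × 2 = 10 (Phototherapy).

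**The plan's own figure.** 15 × 1.2 = 18 and 4 × 18 = 72, as stated. The 15 cannot be reproduced, because no effect size or SD is given. If it came from a four-group ANOVA, it implies an effect of f = 0.554.

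**Assumed, not in the protocol.** Any significant test counts as success. Correlations between times, between sites and between instruments are varied.

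**Formula.** For k independent tests at 5%, the chance of at least one false positive is 1 − 0.95^k. Correlated tests were simulated under no effect anywhere, with one-way ANOVA in four groups of 15; groups of 18 gave nearly the same results. Triples such as 0.5/0.5/0.3 are the correlations between times, sites and instruments.

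| Tests of the primary outcome | k | Independent | Correlated (simulated) |
|---|---|---|---|
| VAS, 3 times | 3 | 1 − 0.95^3 = 14.3% | 12.9%, 11.0%, 8.6% at 0.5, 0.7, 0.9 between times |
| VAS + one algometry summary, 3 times | 6 | 1 − 0.95^6 = 26.5% | 23% at 0.5/0.5/0.3; 15% at a common 0.8 |
| VAS + 10 sites, 3 times | 33 | 1 − 0.95^33 = 81.6% | 65% at 0.5/0.5/0.3; 27% at 0.9/0.9/0.5 |
| VAS + 14 sites, 3 times | 45 | 1 − 0.95^45 = 90.1% | 73% at 0.5/0.5/0.3; 29% at 0.9/0.9/0.5 |

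On the narrow reading of 8 sites, k = 3 × 9 = 27, and 1 − 0.95^27 = 75% if independent.

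The first two rows need no assumption about site-level testing. The last two apply only if each site is tested separately. Only the four-group tests are counted. If each dose were instead compared with placebo at an unadjusted 5%, the six-test figure would be about 50% at 0.5/0.5/0.3.

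**Cost of keeping all six as primary.** Bonferroni gives 0.05/6 = 0.0083 per test. With f = 0.554, power per test falls from 95% to 82% with 60 completers. If all 72 complete, it is 91%.

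**The case against.** The strongest reply is that this is a journal article. A multiplicity rule, or a rule for averaging algometer sites, may stand in a full protocol or analysis plan that is not shown. That is fair: the lack of an adjustment is not itself the fault. What remains is that this document does choose the primary outcome, and chooses two instruments without a deciding time.

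Second, the inflation presumes that one positive result suffices. If both instruments had to succeed, there would be no inflation across instruments. Picking the best of three times would still allow an error of up to 9-14%, the level for one instrument alone. The protocol states neither rule.

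Three stronger readings are tempting, and the protocol does not support them:

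- A reader might infer one definite error rate far above 5%. No correlation is given, so only ranges under stated assumptions are possible.
- A reader might infer 14 separate site tests. The Algometry section describes data collection, not analysis, and 14 is only the upper count.
- A reader might add the within-group follow-up tests to the count. The protocol says: "Intra-group comparisons will be performed using repeated-measures analysis of variance (ANOVA or Friedman’s test), followed by either the Student’s t-test or Wilcoxon’s test". That reads most naturally as testing pairs of times only after a significant overall test. Changes within a group are also not comparisons between groups.

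The time to choose is also open to debate. The Background speaks of "primarily analyzing immediate effect to later assess cumulative dose effects", but as a general research need, and the hypothesis also concerns 24 and 48 hours.

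**Conclusion.** The point holds. The primary outcome is not fixed to one variable at one time, and the plan as written does not hold 5% for its main conclusion when any significant result counts. On that rule the chance of a false primary finding is about 15-27% for six tests, three to five times the nominal level, and 9-14% for VAS alone at three times. The lower ends assume high correlation and the upper ends independence.

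The figure of roughly 30-90% is a conditional worst case. It needs separate testing of 10 to 14 sites, which is stated nowhere, and the Algometry and Phototherapy sections do not agree on the points. The direction of the problem is certain; its exact size is not.

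**What to change.** 1. Name VAS at one stated time as the single primary endpoint, tested between groups at 5%. VAS is the variable behind the sample size. Immediately after treatment would be consistent with the Background, but any one time fixed in advance would serve.
2. Test VAS at the other two times in a fixed order, each at 5% and only if the preceding test is significant. If immediate comes first, the order 24 h then 48 h matches the hypothesis that the effect lasts.
3. Reconcile the point sets in the Algometry and Phototherapy sections. Then define one algometry value per person and visit, the mean over that single set, as the key secondary endpoint.
4. Label site-level, within-group and EMG tests as supportive.

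This is a change of wording and needs no extra participants. Algometry alone could no longer carry the primary claim, and a failed first test would block formal claims at the later times. The Trial status section describes recruitment as under way, and the Blinding section keeps the statistician blinded until the analyses end, so the choice can still be made and dated before results by group are known.

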
The aim of the proposed study is to evaluate the effects of four different doses of phototherapy (0, 2.62, 5.24 and 7.86 Joules) on pain, activity of the masticatory muscles (massester and bilateral anterior temporal) and joint mobility in individuals with temporomandibular disorder (TMD). A further aim is to determine the cumulative effect 24 and 48 hours after a single session. The hypothesis is that individuals with TMD submitted to phototherapy with different light sources (LLLT and LED) contained in a single device with a dose of 7.86 will experience a greater reduction in pain and change in electromyographic activity of the masticatory muscles in comparison to individuals submitted to lower doses and the effects of a single session of phototherapy will be maintained for 24 and 48 hours.

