### Inclusion criteria

All volunteers will have a diagnosis of myogenous TMD based on the RDC/TMD, with moderate to severe pain in the masseter and temporal muscles being rated by an expert dentist. To standardize the sample, the body mass index of all participants must be less than 25 kg/m2, as the amount of adipose tissue between the electrode and surface of the muscle can affect that reading of the electromyographic (EMG) signal [15]. All volunteers must also have an initial pain score greater than 3 points on the VAS [16].

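### The hypothesis is that 7.86 J beats the lower doses, but the only between-group test stated is an omnibus test; pairwise follow-up is stated only within groups

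*Protocol article*

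**What the plan says.** The last paragraph of the Background states a directional comparison between randomised groups: participants treated "with a dose of 7.86 will experience a greater reduction in pain and change in electromyographic activity of the masticatory muscles in comparison to individuals" given lower doses. It adds that the effects of the single session will be maintained for 24 and 48 hours.

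The Data analysis section sets the tests:

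- Within groups: "Intra-group comparisons will be performed using repeated-measures analysis of variance", or Friedman's test, followed by Student's t-test or Wilcoxon's test.
- Between groups: "Inter-group comparisons will be performed using either one-way ANOVA or the Kruskal-Wallis test". No contrast, post-hoc test or trend test follows.
- Factor: "The independent variables will be the different light sources used for phototherapy".
- Level: 5%, with the choice of test depending on the distribution of the data.

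Table 2 shows what separates the active arms. All use one nine-diode cluster, for 20, 40 or 60 s: "Total delivered energy (J) per point 2.62; 5.24 or 7.86". The Sample size section gives a minimum of 15 per group, raised to 18, at α = 0.05 and 95% power. It states no effect size, SD or test.

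**The concern.** The hypothesis needs C (7.86 J) compared with A (2.62 J) and B (5.24 J), and with D (0 J) for efficacy. None of the stated tests makes these comparisons. The between-group test asks whether the four groups are all alike. The tests that look at pairs look only at pairs of times inside one group.

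A significant omnibus test would leave the preferred dose unidentified. A reader would then be drawn to the within-group results, where C may be significant and another group not. That pattern does not test C against the other group. It is also easy to obtain here. The inclusion criteria state that "All volunteers must also have an initial pain score greater than 3 points on the VAS", so some improvement through regression to the mean is plausible in every arm, placebo included.

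At stake is the conclusion about the best dose, which is the purpose of the trial.

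**Working it through.** **1. The plan's own figure.** 15 × 1.20 = 18 reproduces the stated 18 per group. The 15 cannot be reproduced, because no effect size, SD or test is given. I therefore solved backwards, assuming it was sized for the four-group F test.

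- Inputs from Sample size: n = 15 per group, so N = 60; α = 0.05; power 0.95.
- Power = P(F′(3, 56; λ) > 2.769), with λ = N f².
- Power 0.95 requires λ = 18.42, so f = √(18.42/60) = 0.554.

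**2. What a significant omnibus test can mean.** Let placebo have mean 0 and all three active doses the same mean δ, in SD units.

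- SD of the four means = δ√(3/16) = 0.433δ.
- f = 0.554 gives δ = 0.554/0.433 = 1.28.
- The omnibus test rejects 95% of the time, although C is no better than A or B.

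If unplanned pairwise t-tests at 5% were then run after a significant omnibus result, C would differ falsely from A or B in about 9% of trials (simulation, 40,000 runs).

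**3. Power of the contrasts that the hypothesis needs, at the same f.** Two-sided t-test, n = 15 per group, pooled error df = 56.

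- Linear pattern (0, s, 2s, 3s): SD of means = s√1.25, so s = 0.554/1.118 = 0.496. Hence C vs B has d = 0.50 and C vs A has d = 0.99.
- Only 7.86 J works: d = 1.28 for C against each other group.

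| Pattern | Contrast | d | Power at 5% | Power at 5%/3 |
|---|---|---|---|---|
| Linear | C vs B | 0.50 | 27% | 14% |
| Linear | C vs A | 0.99 | 76% | 60% |
| Only C works | C vs B | 1.28 | 93% | 85% |

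In all of these patterns the omnibus power is 95%. It therefore says little about the power to rank the doses.

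**4. Within-group P values as a substitute.** Assume equal true change in all four groups, so no dose effect. Use a two-sided paired t-test in each group with n = 15 (df = 14, critical value 2.145) and noncentrality (change/SD) × √15. Let p be the probability of significance in one group. The groups are independent, so:

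- P(C significant, placebo not) = p(1 − p)
- P(C significant, at least one of the other three not) = p(1 − p³)

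The documents give neither the change nor its SD. I assumed changes of 1.0-1.5 cm and SDs of 1.5-2.0 cm. The four corner combinations are:

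| Change/SD | p (also the chance that placebo alone is significant) | C significant, placebo not | C significant, at least one other not |
|---|---|---|---|
| 1.0/2.0 = 0.50 | 0.44 | 25% | 40% |
| 1.0/1.5 = 0.67 | 0.67 | 22% | 47% |
| 1.5/2.0 = 0.75 | 0.77 | 18% | 42% |
| 1.5/1.5 = 1.00 | 0.95 | 5% | 14% |

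**5. The factor.** Only exposure time, and with it energy, changes across the active arms in Table 2; the laser and LED mix does not. Light source is therefore not varied between them, and dose is.

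**The case against.** The strongest case against runs as follows.

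- **This is a condensed article.** Post-hoc procedures and multiplicity methods are often left to an SAP, which is not shown. That would excuse silence. Here the article states where pairwise follow-up is done and attaches it to the intra-group analysis, while its hypothesis is between groups. The mismatch stands.
- **A reader might infer that the dose conclusion will be drawn from within-group P values and that placebo is ignored.** The text does not support this. A separate inter-group test at 5% is stated, and one-way ANOVA across A to D includes placebo. Regression to the mean acts on all randomised arms and does not bias that test. The rates in step 4 show why within-group results could not fill the gap, not what the plan says it will do.
- **A reader might think that a group-by-time term is required.** It is not. The dependent variables are derived from pre- and post-treatment evaluations, which is compatible with change scores, and a between-group test on change at a given time needs no interaction term.
- **A trend test might be urged mainly for power.** The document gives no ground for a large gain. At the implied f = 0.554, with a linear pattern, a 1-df trend has about 99% power against 95% for the omnibus.
- **The light-source wording** is the article's habitual label for the combined device, and the groups are defined in Joules elsewhere. No stated hypothesis compares light sources. This stands, so it is a wording correction only.

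**Conclusion.** The concern holds as a mismatch between hypothesis and stated tests. The claim that 7.86 J is better than the lower doses has no between-dose test in the Data analysis section. This follows from the text alone and needs no numerical assumption.

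The sizes do rest on assumptions. The 95% rejection with identical active doses assumes that 15 per group was sized for the four-group F test. The rates of 5-25% and 14-47% assume equal true change, 15 per group and change/SD between 0.5 and 1.0. At the upper end of that range the chance that C is significant and placebo is not falls to about 5%, so it would be wrong to call that rate far above 5% throughout.

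The point should be settled before unblinding, because it decides what the trial can conclude about dose. Calling Cohen's d a clinical effect size is a minor matter and does not bear on this conclusion.

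**What to change.** In the Data analysis section:

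1. Name dose group (0, 2.62, 5.24, 7.86 J) as the independent variable in place of light sources.
2. Make the confirmatory analysis between-group, on change from baseline or baseline-adjusted VAS.
3. Prespecify the contrasts C vs A, C vs B and C vs D under Holm or a declared fixed sequence. A linear dose trend may come first, but it does not replace the contrasts.
4. Judge maintenance at 24 and 48 h by the between-group differences at those times, with 95% confidence intervals.
5. Label the intra-group tests descriptive.

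The cost is a few sentences and no new data or patients. The Trial status section says that recruitment is under way, so the change can still be made before unblinding. The downside is lower power per contrast after multiplicity control. With a linear dose response at the implied f, C vs B falls from 27% to 14% under Bonferroni for three contrasts. Holm loses no more than that, and a fixed sequence tests each step at the full 5% but depends on the order chosen. The low figure for C vs B is best acknowledged now, since 15 per group may not separate adjacent doses.

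### The only planned tests between visits are within-arm with no correction named, so a stable effect can appear to fade or grow, and doses to differ in persistence, by chance

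*Protocol article*

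**What the plan says.** All references are to the protocol article.

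- **Data analysis, within arms:** "Intra-group comparisons will be performed using repeated-measures analysis of variance" or Friedman's test, "followed by either the Student’s t-test or Wilcoxon’s test". The visit pairs to be tested are not listed.
- **Data analysis, threshold:** "The level of significance will be set to 5" per cent. No correction is named for the follow-up tests.
- **Data analysis, between arms:** "Inter-group comparisons will be performed using either one-way ANOVA or the Kruskal-Wallis test". This compares arms, not visits.
- **Abstract, Methods/Design:** assessments at "baseline and immediately after, 24 h after and 48 h after phototherapy". On the arms: "Three groups will be submitted to a single session of phototherapy with different light sources, and one group will receive placebo therapy".
- **Background, hypothesis:** "the effects of a single session of phototherapy will be maintained for 24 and 48 hours".

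No sentence says which test will decide the maintenance hypothesis.

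**The concern.** A statement about persistence needs either a comparison between visits or a comparison with placebo at the late visits. The article names between-visit tests only inside each arm, so these are the natural route to the maintenance hypothesis.

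Requiring a significant repeated-measures ANOVA first holds the within-arm error near 5% only when all four visits have the same mean. The trial expects pain to fall after the session. Once it falls, the omnibus test is likely to be significant because of the baseline visit alone. The comparisons among the immediate, 24 h and 48 h visits then run at an unprotected 5% each.

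Two misreadings could follow. An arm whose effect is stable may be reported as losing or gaining effect between visits. And because each arm is tested separately, one dose may look persistent and another not, when no test has compared them.

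**Working it through.** **The plan's own figures.** The article states no error rate for the within-arm tests, so there is none to reproduce. The Sample size section gives 15 per group plus 20%: 15 × 1.2 = 18, and 4 × 18 = 72, as stated. Both 15 and 18 per arm are used below.

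**Inputs from the article.** Four visits, four arms (three active, one placebo), a 5% level, and an omnibus test followed by paired tests.

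**Assumed inputs.** The article gives no SD, correlation or effect size. I assume a VAS SD of 2 cm, within-person correlation 0.5 between any two visits, two-sided tests, and a drop of 1, 1.5 or 2 cm that is identical at all three post-treatment visits. I also assume that all visit pairs are tested.

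**Step 1: count the tests.** Visit pairs per arm: 4 × 3 / 2 = 6, so 6 × 4 = 24 per outcome. Under a constant drop, the three pairs with baseline are truly different. The three pairs among post-treatment visits are truly null.

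**Step 2: simulate one arm.** Run the repeated-measures ANOVA at 5%. If it is significant, run the paired t-tests at 5%. Count any rejection among the three null pairs. Call this rate p.

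**Step 3: combine arms.** Arms are independent, so the chance over k arms is 1 − (1 − p)^k.

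| Constant drop, 15 per arm | p per arm | Three active arms | Four arms |
|---|---|---|---|
| 1 cm | 10% | 1 − 0.90³ = 27% | 1 − 0.90⁴ = 34% |
| 1.5 cm | 12% | 1 − 0.88³ = 32% | 1 − 0.88⁴ = 40% |
| 2 cm | 12.5% | 1 − 0.875³ = 33% | 1 − 0.875⁴ = 41% |

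Simulation error moves these by about a point, which gives the ranges 10-13%, 27-33% and 34-42%. With 18 per arm the four-arm figure is 36-41%.

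**Step 4: sensitivity.**
- Correlation 0.3 or 0.7 at a 1.5 cm drop: about 39% and 42% over four arms.
- Only immediate-versus-24 h and immediate-versus-48 h counted: about 27-32% over four arms.
- No change at any visit, all six pairs counted: the omnibus test works as intended, with p about 5% per arm. Over four arms, 1 − 0.95⁴ = 18.5%.
- Only the three comparisons with baseline tested: under a constant drop no tested pair is null, so this error cannot occur.

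**Step 5: the opposite error, a false claim that the effect lasted.** Take no true effect at 24 h and 48 h, with or without a real immediate change, and require both late visits to differ from baseline. At correlation 0.5 this happens in 0.5-0.9% of arms and in about 2-4% of trials over four arms. If correlation instead decays with time (0.7 between adjacent visits), it is just under 2% per arm and up to 7% over four arms.

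**The case against.** Several points on the other side are sound.

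- **The pairs are not listed.** If only comparisons with baseline are made, the constant-drop figures do not apply. This stands, and the result is conditional on it.
- **The hypothesis is not tied to these tests in words.** This also stands. The link is an inference from their being the only named tests between visits. The planned between-group test could address late visits, but the article does not assign it that role.
- **A correction may sit in an analysis plan that is not shown.** Possible. The point therefore does not rest on silence alone. The stated method judges change within each arm separately, and adjusting p-values would not turn that into a comparison of persistence between doses or with placebo.
- **Four arms includes placebo.** The four-arm figure needs placebo patients to improve as well. For phototherapy alone the three-arm figure, 27-33%, is the relevant one.

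A reader might infer that a conclusion of maintenance carries a 30-40% false-positive risk. The documents do not support that. Under a stable effect the null pairs are those between post-treatment visits, and rejecting one of them argues against maintenance. The false claim of maintenance is the small figure in Step 5.

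A reader might also compound the risk over VAS and algometer. Treating two pain measures in the same women as independent has no basis in the article, so the figures here are for one outcome.

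**Conclusion.** The point holds as a weakness in how persistence would be judged. As written, the within-arm sequence can report a stable effect as fading or growing in about 10-13% of arms, with at least one such report in 27-33% of trials over the active arms and 34-42% over all four. This depends on a real and constant fall in pain, all visit pairs being tested, and the assumed SD and correlation. Correlation matters little over 0.3 to 0.7. If nothing changes at any visit, the risk of any false difference is about 5% per arm and 18-19% over four arms.

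The practical harm is that doses may appear to differ in persistence by chance. The calculation does not show a high risk of falsely declaring the effect maintained.

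**What to change.** Change one sentence in Data analysis: report within-arm changes descriptively, as mean change with 95% confidence interval, and judge persistence by the active-minus-placebo difference at 24 h and at 48 h, each with its confidence interval.

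A multiplicity correction over all 24 within-arm comparisons is not a good substitute. Where maintenance is read from a non-significant difference between visits, a stricter threshold makes real fading easier to miss. With true drops of 2, 1.25 and 0.5 cm in all four arms, and the same SD and correlation, detection of the loss between the immediate and 48 h visits falls from 74% uncorrected to 27% under Holm.

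The cost is that within-arm p-values no longer support conclusions. No new data or participants are needed. The between-arm estimate will show its imprecision. With SD 2 cm and correlation 0.5, the SD of a change is 2 × √(2 × (1 − 0.5)) = 2 cm. The standard error of a difference is then 2 × √(2/15) = 0.73 cm with 15 per arm and 2 × √(2/18) = 0.67 cm with 18.
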